## Abstract

**Background:**

Public adherence to cancer screening guidelines is poor. Patient confusion over multiple recommendations and modalities for cancer screening has been found to be a major barrier to screening adherence. Such problems will only increase as screening guidelines and timetables become individualized.

**Objective:**

We propose to increase compliance with cancer screening through two-way rich media mobile messaging based on personalized risk assessment.

**Methods:**

We propose to develop and test a product that will store algorithms required to personalize cancer screening in a central database managed by a rule-based workflow engine, and implemented via messaging to the patient’s mobile phone. We will conduct a randomized controlled trial focusing on prostate cancer screening to study the hypothesis that mobile reminders improve adherence to screening guidelines. We will also explore a secondary hypothesis that patients who reply to the messaging reminders are more engaged and at lower risk of non-adherence. We will conduct a randomized controlled trial in a sample of males between 40 and 75 years (eligible for prostate cancer screening) who are willing to receive text messages, email, or automated voice messages. Participants will be recruited from a primary care clinic and asked to schedule prostate cancer screening at the clinic within the next 3 weeks. The intervention group will receive reminders and confirmation communications for making an appointment, keeping the appointment, and reporting the test results back to the investigators. Three outcomes will be evaluated: (1) the proportion of participants who make an appointment with a physician following a mobile message reminder, (2) the proportion of participants who keep the appointment, and (3) the proportion of participants who report the results of the screening (via text or Web).

**Conclusions:**

We believe that the use of centralized databases and text messaging could improve adherence with screening guidelines. Furthermore, we anticipate this method of increasing patient engagement could be applied to a broad range of health issues, both inside and outside of the context of cancer. This project will be an important first step in determining the feasibility of personalized text messaging to improve long-term adherence to screening recommendations.

## Introduction

Cancer is the second most common cause of death in the United States. In 2012, it is estimated that 1.6 million new cancer cases will be diagnosed and 577,190 Americans will die from cancer [1]. At least half of all new cancer cases can be prevented or detected by screening. Cancer screening not only prevents unnecessary cancer deaths, but it also can reduce the morbidity of cancer before it progresses to more advanced aggressive stages [2]. Despite the benefits of cancer screening, public adherence to guidelines for cancer screening is often poor. *Healthy People 2020*, the 10-year health agenda released by the US Department of Health and Human Services, reported only modest screening rates for breast cancer, cervical cancer, and colorectal cancer. For example, only 59% of adults reported being up-to-date with colorectal cancer screening [3].

Although screening can be beneficial, it is important that patients consult their doctor to determine which types of screening are appropriate for them. Screening guidelines vary widely depending on the type of cancer, patient age, gender, ethnicity, and family history [2]. Patient confusion over multiple recommendations and modalities for cancer screening has been found to be a major barrier to screening adherence [4]. Complicating this matter is the fact that cancer screening schedules often need to be dynamically adjusted for each individual based on previous screening results and comorbidities. For example, the recommended interval between prostate-specific antigen (PSA) tests depends on the most recent PSA level, with longer intervals (ie, less frequent testing) for men with lower PSA levels [5]. Similar dynamic screening and intervention algorithms have been suggested for other types of cancers, such as breast cancer [6,7].

Patient engagement and reminders improve adherence to cancer screening guidelines [8]. The Community Preventive Services Task Force, an independent group of public health experts appointed by the Director of the Centers for Disease Control and Prevention, recommends using client reminders to increase cancer screening based on strong evidence of effectiveness; reminders have been shown to increase mammography screening by a median of 10% and increase colon cancer screening by a median of 15% [9]. Although short message service (SMS) text-based reminders sent to mobile phones have not been studied specifically for cancer screening, SMS-based reminders have been demonstrated to reduce patient appointment no-shows by up to 40% [10], and reduce nonadherence with chronic disease follow-ups by up to 35% [11]. SMS reminders have been used successfully in driving positive behavior changes in areas such as medication compliance [12], weight loss [13], smoking cessation [14], and physical activity promotion [15]. A recent review of the use of SMS technology for health behavior change interventions found that SMS interventions yielded positive behavior changes in 93% of studies reviewed. The authors found that SMS was an effective delivery method for tailored advice and reminder messages for behaviors such as smoking cessation, diabetes self-management, and medication compliance [16].

In the United States, mobile messaging solutions have the potential to reach vast numbers of patients. It is estimated that 82% of American adults have cell phones, with the penetration rate skewed higher among African American and Latino populations [17]. A survey conducted in 2010 concluded that 79% of Medicaid patients with mobile phones are active SMS users [18]. Although this project focuses on prostate cancer screening, the product we propose to develop and test has wide-ranging implications for adherence to screening for many other types of cancers and for chronic disease management.

In this project, we propose to develop technology-based interventions, specifically, automated reminders sent to consumer mobile phones to help patients stay motivated and adherent with their personalized cancer screening schedules. The interventions are based on the theory of planned behavior [19], in particular the unified theory of acceptance and use of technology (UTAUT) [20] and the Patient Activation Measure (PAM) [21]. The UTAUT is a theoretical model and instrument used to assess the likelihood of user acceptance for new technology that posits that performance expectancy, effort expectancy, social influence, and facilitating conditions are direct determinants of use [20]. The UTAUT instrument is widely used to evaluate the factors affecting adoption of new technology solutions [22]. Patient activation refers to a person’s ability and willingness to manage their health and health care [23]. The PAM is a 22-item assessment used to evaluate an individual’s knowledge, beliefs, and confidence in managing their health [21]. High patient activation has been shown to be positively associated with utilization of preventive services, self-management behaviors, medication adherence, self-reported quality of care, and perceived doctor-patient communication [24-26].

We will conduct a randomized controlled trial to study the hypothesis that mobile reminders improve adherence to screening guidelines. Mobile messaging is an intervention that can be applied to a large population at low cost because it can be easily automated. We will also explore a secondary hypothesis that patients who reply to the messaging reminders are more engaged and at lower risk of nonadherence. The impact is that low-cost mobile messaging could be used as a signaling mechanism to predict patients with high risk of nonadherence, and resources could be optimized to target those patients for more intensive follow-ups.

In this project, we focus on prostate cancer to examine proof of principle for our general approach. We will use screening algorithms adapted from evidence-based prostate screening guidelines and multimedia content tailored for mobile phone use. We plan to subsequently develop and test algorithms for other types of common cancers, such as breast cancer and colorectal cancer.

## Methods

### Study Objectives

Our primary hypothesis is that use of the mobile messaging reminders will increase patient adherence to screening. To evaluate this hypothesis, we will conduct a randomized controlled trial in a sample of males between 40 and 75 years (eligible for prostate cancer screening) who are willing to receive text messages, email, or automated voice messages. The sample will be recruited from male clinic patients who may or may not be in the clinic for prostate-related problems at the time of recruitment.

### Eligibility Criteria

The project will solicit participation from men aged 40-75 years of all ethnicities who visit 3 designated primary care clinics or 2 area community health fairs in Texarkana and New Boston, Texas, and Hope, Arkansas. No one will be excluded from the study on the basis of race/ethnicity or disability. Participants must have Internet access at home or at work and be willing to receive message-based communications on their choice of communication channels, including mobile messaging, email, and automated voice messages. Participants must be willing to pay for any communication costs charged by their wireless carrier, Internet provider, or phone company. Participants will be excluded if they have been diagnosed with prostate cancer, have had a PSA test in the previous 12 months, or have a current appointment for prostate cancer screening.

### Recruitment

All eligible participants will be given a study information sheet upon check-in at the clinic. The information sheet will include a brief description of the study, including the study purpose, procedure, and relevant risks and benefits. The information sheet will instruct interested participants how to enroll in the study through a secure Web portal where they will give their informed consent and mobile phone number to the research team. When available, a trained research nurse will explain the details of the study to eligible participants, answer any questions, and give the participants the opportunity to enroll during check-in at the clinic. Depending on their communication preference stated at the time of sign-up, participants will receive a text message or email on their phone or a voice message asking them to confirm that they would like to participate in the study. Patients must respond yes to this message to enroll in the study.

### Study Procedures

After initial recruitment, participants will be asked to complete a brief questionnaire about their basic sociodemographic details and relevant health history, as well as a Technology Acceptance Model questionnaire [22] and the PAM [21] to measure patient engagement in health care. Participants will be randomly assigned to the intervention or the control group using a random number generator. Randomization will be implemented automatically by a secure password-protected algorithm at the time the user signs up. This guarantees that assignment cannot be predicted before or changed after the participant is registered in the study. All participants will be asked to schedule prostate cancer screening at the clinic within the next 3 weeks, but only the intervention group will receive reminders and confirmation communications for (1) making an appointment, (2) keeping the appointment, and (3) reporting test results back to the investigators.

A flowchart of the reminders/confirmations and the expected responses from participants is illustrated in Figure 1.

**Figure 1 figure1:**
[figure not shown]
Study flowchart.

### Screening Reminders

A screening schedule reminder will be sent to remind the participant to make an appointment for the screening test. One week after the participant confirms his appointment, the system will ask the participant whether he has seen the doctor yet. This message will repeat every 2 weeks until the participant confirms that he has kept the appointment and seen the physician. Then the system will ask the participant whether he has received his test results. This message will repeat every 3 days until the participant confirms that he has received the test results. The participant will then be asked to report back his test results to the research team using the secure Web portal.

In addition to the messages, we will also provide patient education and health promotion materials to the participants as part of the communication process. Upon initial registration on the secure website, a short video will explain the importance of prostate cancer screening and what to expect from the screening tests to both the control and intervention group participants. Once the intervention group participants confirm and report back their test results, another short video will explain ranges and meanings of test results, and the preventive actions the participant can take to reduce prostate cancer risk.

At the end of the study period, all patients will be contacted again through their preferred communication channels as indicated at sign-up (eg, text message, email, or voice message). All participants will be asked to report whether they have made appointments for prostate screening, kept their appointments, and reported back the test results. All participants will also be asked to complete a second questionnaire on the secure website that is a repeat of all initial questionnaire items except the sociodemographic items. The study period will last 8 weeks. Participants will receive a US $10 gift card as compensation for their participation in this study.

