### Evaluation

Three outcomes will be evaluated: (1) the proportion of participants who make an appointment with a physician following a mobile message reminder, (2) the proportion of participants who keep the appointment, and (3) the proportion of participants who report the results of the screening (via text or Web). To facilitate comparison with existing literature, each outcome will be examined independently as a separate outcome. Adherence rates in the intervention and control group will be compared using the Fisher exact test.

Our second goal is to examine user adoption, identify factors that foster or hinder adoption, and identify patients who are at high risk of nonadherence. Examination of these questions will utilize data from the intervention group only. We hypothesize that those who respond to texts will show higher levels of adherence and patient activation than those who do not respond. For these analyses, we will focus on both user responses to reminders and adherence, which will be treated as a continuous variable by counting the total number of adherence behaviors (eg, made the appointment, kept the appointment, and followed up after results). Factors that foster or hinder adoption will be examined both preintervention and postintervention utilizing all available measures, particularly those related to technology acceptance factors defined in the UTAUT model. Examination of user adoption and factors fostering or hindering adoption will be accomplished through ordinary least-squares regressions. The UTAUT survey questionnaires are designed to measure 4 latent factors that drive technology adoption: performance expectancy, effort expectancy, social influence, and facilitating conditions. The first 3 factors are linked to behavior intention, another latent factor. We will conduct confirmatory analysis using structural equation modeling technique against the data. This will result in a path diagram that weights each latent factor’s contribution to user adoption of this technology. The analysis will help to identify the key drivers of user adoption and give the team directions for further product improvements.

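### Made and kept appointments are self-reported, and only the intervention arm is asked about them before the end of the study; the between-arm tests are not limited to the contact that both arms share

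*Protocol article*

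**What the plan says.** Under Study Procedures, every man is asked to book screening at the clinic within 3 weeks. The messages, however, go to one arm: "only the intervention group will receive reminders and confirmation communications for (1) making an appointment, (2) keeping the appointment, and (3) reporting test results".

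Under Screening Reminders, the intervention arm receives a reminder to book. One week after a man confirms his appointment he is asked whether he has seen the doctor: "This message will repeat every 2 weeks until the participant confirms that he has kept the appointment and seen the physician". He is then asked whether he has his results: "This message will repeat every 3 days until the participant confirms that he has received the test results".

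The same section describes one query common to both arms: "At the end of the study period, all patients will be contacted again through their preferred communication channels as indicated at sign-up". At that contact, "All participants will be asked to report whether they have made appointments for prostate screening, kept their appointments, and reported back the test results". On duration it says: "The study period will last 8 weeks".

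Under Evaluation, the three outcomes are the proportions making an appointment, keeping it and reporting results. Each is examined separately, and the arms are compared by the Fisher exact test. The section does not say whether interim confirmations, end-of-study answers or both feed the test, nor how men who do not answer are counted. The article describes no comparison with clinic records.

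**The concern.** In the intervention arm the messages do two jobs. They are the treatment, and they also collect data on the outcome. Controls have no counterpart to the second job.

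Take two men who behave identically: each keeps an appointment and neither answers the final contact. If interim confirmations count, the intervention man who confirmed earlier is recorded as adherent, while the control has no data. In addition, the kept-appointment prompt stops only when the man confirms, which may encourage a confirming answer. Participants know whether they are receiving reminders.

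What is at stake is the primary hypothesis, that reminders increase adherence to screening. A difference in recorded adherence could come partly or wholly from a difference in recording. Sample size does not protect against this: the spurious difference stays the same as the trial grows, and the test becomes more likely to call it significant.

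**Working it through.** **Who is asked what, and when**

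| Outcome | Intervention arm, during follow-up | Control arm, during follow-up | Both arms, end of study |
|---|---|---|---|
| 1. Made appointment | Booking reminder and confirmation; no repeat stated | None described | Asked |
| 2. Kept appointment | Asked 1 week after the appointment is confirmed, then every 2 weeks until confirmed | None described | Asked |
| 3. Reported results | Asked every 3 days until receipt of results is confirmed, then asked to report them | None described | Asked |

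The asymmetry is clearest for outcome 2. It exists for outcome 1, but without documented repetition. Outcome 3 is different in kind. The outcome is itself an act of reporting, so there is no separate behaviour to record incompletely. It is prompted in one arm only, so it partly measures response to the prompt.

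**Illustration of size for outcomes 1 and 2**

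The article gives no sample size, significance level, event rate or response rate, so there is no figure of its own to reproduce. Every input below is an assumption:

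- True adherence rate p, the same in both arms (no effect): 30% or 50%.
- Capture, meaning the probability that an adherent man is recorded as adherent: r_I = 90% in the intervention arm; r_C = 60% to 80% in controls.
- Men not captured are counted as not adherent.
- Two-sided Fisher exact test at 5%, with 50, 100 or 200 men per arm.

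Observed rate = p × r, so spurious difference = p × (r_I − r_C).

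- Smallest case: 0.30 × (0.90 − 0.80) = 0.27 − 0.24 = 3 points.
- Largest case: 0.50 × (0.90 − 0.60) = 0.45 − 0.30 = 15 points.

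Probability that the Fisher test rejects although there is no effect, by exact enumeration:

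| p | r_I v r_C | Observed rates | Difference | 50 per arm | 100 per arm |
|---|---|---|---|---|---|
| 30% | 90% v 80% | 27% v 24% | 3 points | 4.0% | 5.5% |
| 30% | 90% v 60% | 27% v 18% | 9 points | 13.5% | 27.3% |
| 50% | 90% v 80% | 45% v 40% | 5 points | 5.6% | 8.9% |
| 50% | 90% v 60% | 45% v 30% | 15 points | 27.2% | 53.5% |

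At 200 per arm the range over the same assumptions is 8.6% (first row) to 85.4% (last row).

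With equal capture of 90% in both arms, as one common source would aim for, the rate is 3.1% to 3.9% at 50 to 100 per arm, below the nominal 5%.

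For scale, the Introduction cites median gains from reminders of 10% for mammography and 15% for colon cancer screening. The upper part of the spurious range is of similar size.

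**The case against.** The strongest reply is that a symmetric measurement already exists. The end-of-study question goes to both arms and is the only outcome query described for both, so it is the natural source for the comparison. No sentence says that interim confirmations enter the Fisher tests. The Evaluation section discusses user responses to reminders within the intervention-only analyses. The article is condensed and its flowchart is not available here, so the data source, or a records check, may be specified elsewhere.

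Much of this stands. A reader might infer that a false effect is bound to appear and can never be separated from a true one. The article does not support that: if only the common contact is analysed, the outcome query is the same in both arms. Nor is it certain that capture will be better in the intervention arm, since frequent messages could reduce replies to the final contact. A reader might also infer that all three outcomes are repeatedly prompted and mis-captured. No repeat is documented for making an appointment, and the capture argument does not fit result reporting.

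It does not dispose of the point. The article sets out how outcomes are collected, that description differs by arm, and nothing restricts the tests to the shared contact. Outcome 1 is even worded as making an appointment after a mobile reminder, which does not point to the end-of-study answer alone. Restricting to that answer would also leave a smaller problem if response to it differs by arm.

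**Conclusion.** The concern holds for outcomes 1 and 2, and most clearly for outcome 2. These are self-reports with no record check described, solicited during follow-up in one arm only, and the between-arm tests are not confined to the contact that both arms receive. If interim confirmations count, better capture can pass for better adherence.

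The size is not known. The 3 to 15 points and the false-positive rates rest wholly on assumed capture rates, true rates, arm sizes and a 5% level. In the mildest case with 50 per arm there is no inflation (4.0%). The figures show that the mechanism can matter, not that it will do so in this trial. The direction favours the intervention only if capture is higher in that arm.

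For outcome 3, a difference between arms would show response to prompting and should not be read as evidence of greater screening adherence.

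**What to change.** For outcomes 1 and 2, use one source and one time point in both arms.

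- **Preferred:** the participating clinics' scheduling and visit records at week 8, extracted without knowledge of allocation. This needs consent to record access and a data extraction from the three clinics. Visits elsewhere would be missed, possibly including those of men recruited at the two health fairs, and it should not be assumed that the loss is equal in both arms.
- **If records cannot be obtained:** use only the end-of-study answers, with identical wording and the same number of contact attempts in each arm, and exclude interim confirmations from the between-arm tests. Report response to that contact by arm and add a sensitivity analysis for non-response. Counting non-responders as not adherent does not by itself remove the bias if response differs by arm. The cost is a change of wording plus the extra analysis.

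Report outcome 3 as an engagement measure. Clinic visit records cannot supply it. Keep the interim replies for the intervention-only analyses, where they are useful and raise no between-arm problem.
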